## Management of special aspects and problems

### Parallel somatic treatments

Parallel to the psychosomatic interventions, the patients will often take further diagnostic and treatment measures, these are partly not even made transparent at the beginning. The intervention has a goal of setting a „new beginning“ in the disturbed relationship of the patient with the health care system and tries to encourage cooperation with the patient and with the co-treaters. Making somatic treatment measures transparent or possibly doing without them is mildly positively connotated by the therapist. Doing without parallel treatments is not demanded, but in cases of apparent (financial) self-damaging treatments a clear opinion is expressed if necessary. The family doctor will receive written information about the planned treatment within the study at the beginning thereof. Furthermore, the family doctor will be contacted if necessary during the intervention, but in any case at its ending.

### Parallel pharmacologic treatments

The attitude on this is analogous: parallel medication, whether somatic, analgetic or e.g. antidepressive, will be accepted at the beginning, if necessary, it will be worked towards taking medicine according to plan and not according to need. Transparency and possible rejection are mildly connotated in a positive way, only in case of clearly not indicated drugs (e.g. opiates, benzodiazepines, fluspirilene) a clear opinion is expressed.

### Repeated assurance that there is no or no sufficient organic reason to explain the complaints

Even though the intervention is not primarily aimed at patients with hypochondriasis in the stricter sense, it may happen in the course of the intervention that patients repeatedly urge the therapist to tell them that they do not have a severe illness „for reassurance“ and ask him to undertake further investigations. How to deal with this behaviour depends on the phase, on how to assess the stability of the helping alliance and how to assess the structural vulnerability of the patient.

Initially and in less stable situations, a respective assurance that they do not suffer from a severe illness might be helpful. Later on and in more stable situations, it might be agreed upon with the patient that there will be no assurance and he/she has to endure the triggered fear until it eases away. (It might be necessary to include the relatives into this agreement).

### **Management of „re-somatization“**

During the course of a therapy, it happens almost regularly that distinctively somatoform patients increasingly complain about their symptoms and the feared organic reasons thereof, and all insights into the situative and affective contexts seem to be lost. In this situation, it is important to accept this re-somatized offer as currently necessary for the patient and not to confront the patient with the seemingly lost insights, and at worst in a disappointed and reproachful way. When the therapist maintains an accepting attitude, the patient will sooner be able to use these insights again.

### **Management of „superficial psychologization“**

If the patients soon talk only about their intrapsychic and general relationship problems and spontaneously do not mention the symptoms and impairments anymore or do just seldom mention them, the therapist must actively ask about them, as there is the risk in this constellation that the psychologization stems from a latent loss of self esteem or subordination under the therapist and is not the consequence of a change of the symptom in the context of current life.

### **Management of impending drop-out**

Owing to the described tendency for repeated frustration experiences in treatments, partially after a previous idealization of the therapist, and owing to the often low tolerance level of the patients to bear with these frustrations in the therapeutic relationship, it might happen very soon that the patient wants to stop the therapy. If the patient indicates that he/she wants to stop the therapy, the therapist should firstly discuss the advantages/disadvantages of an early ending with the patient, and not urge him to continue with the therapy. In doing so, the therapist should emphatically deal with the patient's frustration and, together with the patient, develop hypotheses regarding affects and possibly real fears or fears based on transference and discuss them with the patient. Distinctively negative transferences should be actively talked about. In case the patient just misses the session, the therapist should write to the patient and suggest another appointment.

### **Management of missed appointments**

At most 2 missed appointments can be made up for by additionally agreed appointments, regardless of the reason. In case of a missed appointment without excuse, this will be explicitly talked about regarding its meaning for the treatment in the next session.

## **Supplement 3b: Guideline for Control Group intervention**

### **Enhanced Medical Care**

#### **General notes**

In this trial, enhanced medical care is treatment as usual with additional definition of the appointment structure and the communicative strategies in dealing with the patient. The latter features should enhance homogeneity of treatment in the control group across trial sites and also enhance the likelihood of continuing patient participation.

In general, treatment in this arm of the study aims at alleviating pain-related lead symptoms and disabilities. It is performed by the physicians working in the university-based somatic outpatient treatment units that collaborate with the psychosomatic departments at the respective study sites.

The guideline encompasses three aspects: appointment structure, symptom-oriented measures and physician-patient communication. The physicians in charge of the respective somatic treatment unit will supervise the treatment. A workshop will be held with all physicians involved in the study to acquaint them in detail with the procedures.

#### **Appointments**

After being screened and interviewed either in a somatic inpatient or outpatient setting and after entering the study, patients in this study arm will have at least three appointments with the physician at the somatic outpatient treatment unit, e.g. a pain center. The respective appointments are six weeks apart at most. Additional appointments are possible, as needed.

- the emphasis of the first appointment is on negotiation of diagnosis and treatment plan
- the emphasis of the second appointment is on interim results and adjustment of treatment measures
- the emphasis of the third appointment is on planning and negotiating the future course of treatment

The amount of time spent during the appointments will vary according to clinical needs.

The patients will be encouraged, but not obliged to withhold treatment with other specialists at the same time.

#### **Symptom-oriented measures**

As type of lead symptoms and specific treatment setting vary between patients and sites, this guideline cannot be symptom-specific in the strict sense. However, physicians will follow the symptom-specific treatment guidelines published by their respective scientific society within the AWMF (working group of German scientific medical societies).

There are some common principles underlying the different guidelines for treating frequent symptoms like headache, back pain, muscular or lower abdominal pain.

These common principles guide treatment also in this arm of the study, they are as follows:

- competent exclusion of relevant organic causes underlying the symptoms
- treatment of underlying organic causes, when relevant
- rational alleviation of pain and other symptoms by pharmacologic means, including analgesics, but also other types of drugs like muscle relaxing agents, regulators of bowel movement frequency etc.
- additional use of physiotherapy where indicated
- additional use of psychotherapy where indicated
- encouragement of activation rather than rest
- change of therapeutic strategy in case of insufficient symptomatic success after a pre-defined period of time

The physicians taking part in this arm of the study are explicitly encouraged to use the same guideline-based principles they use in treating patients with these lead symptoms outside the study, including criteria for sending patients to psychotherapy.

## **Physician – patient communication**

Definition of physician-patient communication aims at the following

- to avoid iatrogenic factors in the communication that potentially contribute to the persistence of symptoms and illness beliefs
- to ensure active cooperation of the patient in the treatment process
- to enhance homogeneity of treatment across study sites and physicians
- to enhance patient adherence to treatment

The following components should be included in communicating with the patient:

- information about the diagnoses, including the research diagnosis of multisomatoform disorder
- information about treatment alternatives, including self help strategies and complementary medicine
- enquiry about patient's treatment expectations
- negotiation of treatment decisions ("shared decision")

Principles of patient-centered care, including mutual respect and openness for differing views, should underlie these topics. The practice guideline "Defining the patient-physician relationship for the 21st century" (Johns Hopkins; American Healthways 2004) will be distributed and used as a common reference at all study sites.

## **Supplement 5: Methods for Psychophysiological Measurements**

### **Autonomic measurement**

All patients both from the treatment and the control group will be assigned to psychophysiological assessment during a stress test before and after the intervention period. Pre-test as well as post-test anxiety and stress levels will be assessed using a rating of subjective units of discomfort (SUD) on a scale ranging from 0 to 10 (Wolpe 1969). After attachment of the ECG chest-belt (Polar S810) the Stroop-test will be explained to the patients followed by a 2-min training period. Pre-test stress-levels and anxiety will be assessed. Then 5 min of rest without any task will follow where the last 2 minutes will serve as Baseline 1. Stroop test will be applied with duration of 5 minutes followed by a recovery period of 3 minutes. Post-test stress-levels and anxiety will be assessed by SUD ratings immediately after the recovery period. Another 5 minutes of rest follow where the last 2 minutes will serve as Baseline 2.

A time series of inter-beat intervals with a time-resolution of 1000 Hz will be generated from the wireless transmitted ECG signal. HR will be calculated as a mean value for each measuring condition of 2 min duration. HRV will be calculated both in time domain (RMSSD) as well as in frequency domain (HF-HRV) according to published standards (Task Force of the European Society of Cardiology and the North American Society of Pacing and Electrophysiology 1996). HRV-values will be statistically controlled for age, body mass index and for breathing frequency as derived from peak HF-frequency. Due to the expected skewness of data, RMSSD will be logarithmically transformed for statistical comparison. HR and HRV reactivity to Stroop-test will be calculated by subtracting measures during Stroop-test levels with the mean of baseline 1 and baseline 2.

A repeated measures analysis of variance (ANOVA) model with the between subjects factor group (treatment vs. control group), the within subjects factor time and the covariates sex and age will be used for examination of HR and HRV during baseline, stress test and for reactivity scores.

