The „Helpful Alliance Questionnaire“ (Luborsky 1984, German Version: Bassler et al. 1995) is a brief (12 Items) questionnaire for the assessment of perceived therapeutic relationship and therapeutic process. It will be answered as well by the patient as by the therapist and allows interpretation of potentially relevant moderators of therapy outcome (t1).

- **Heart rate variability**

HRV measurement and analysis equipment will be present at each centre. Time-domain (RMSSD) and frequency domain (HF-HRV) analysis will be performed during a stress test

with the emotional stroop paradigm (detailed description of methods see Supplement 5). (t 0, t 1, t 2)

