##### **b) The follow-up for subjects withdrawn from interventional treatment/trial treatment**

- The follow-up for patients who are withdrawn from the interventional treatment will be identical to the follow-up of completers. These patients will be included in the intention-to-treat analysis.

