**7.2. Methods and timing for assessing, recording, and analysing of efficacy parameters**

Efficacy parameters will be assessed before and after the treatment period and after one year. Most efficacy parameters are self-report data. In addition, there will be an assessment of psychophysiological measurements at three month.

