### 9.7. Selection of subjects to be included in the analyses (e.g. intention-to-treat, all randomized subjects, all eligible subjects, evaluable subjects.)

The study population will be as follows:

- Intention- to- treat- population  
This population consists of all subjects randomised, irrespective of whether they received the

experimental or control intervention. Subjects will be analysed according to the intervention to which they have been randomised.

- Per- protocol population  
This population is the subset of all subjects included in the trial which excludes those subjects who had a major protocol deviation.

The efficacy analysis with primary and secondary endpoints criteria will be done in the intention-to- treat population.

In addition, for informative purposes, a less conservative analysis based on the per- protocol- population will be done for the primary and secondary endpoints.

Conclusions of the trial will be based only on the intention- to- treat population.

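### The repeated-measures ANOVA for heart rate variability treats the pre-treatment value as an outcome instead of a covariate, which costs precision that baseline adjustment would recover for free

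*Protocol*

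**What the plan says.** Supplement 5 (Autonomic measurement) specifies "A repeated measures analysis of variance (ANOVA) model with the between subjects factor group", and continues: "the within subjects factor time and the covariates sex and age will be used for examination of HR and HRV during baseline", followed by the stress test and the reactivity scores. The pre-treatment HRV value, centre and setting are not in the model. An earlier sentence of the same supplement says HRV will be controlled for age, body mass index and breathing frequency, which is a different covariate list.

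The visits at which HRV is measured are described in three ways:
- Section 4.1 lists HRV as a secondary endpoint, measured "with the emotional stroop paradigm (detailed description of methods see Supplement 5). (t 0, t 1, t 2", that is, at three time points.
- Supplement 5 says patients "will be assigned to psychophysiological assessment during a stress test before and after the intervention period", that is, at two.
- Section 7.2 says "In addition, there will be an assessment of psychophysiological measurements at three month".

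On populations, section 9.7 states: "The efficacy analysis with primary and secondary endpoints criteria will be done in the intention-to- treat population". It defines that population by randomisation: "This population consists of all subjects randomised, irrespective of whether they received the" experimental or control intervention. Section 5.3 says of patients withdrawn from the intervention: "These patients will be included in the intention-to-treat analysis". The missing-data rule in section 9.5 covers the primary endpoint only.

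Section 4.8 stratifies randomisation by hospital and setting, and the primary model in section 9.1 carries both as random effects.

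**The concern.** HRV is a listed secondary endpoint, and objective (b) in section 3 names it as a mediator of change, so the precision of its arm contrast matters for the mechanistic part of the trial. A pre-treatment value placed among the outcome levels can do two things. If treatment is tested by the group-by-time term, baseline information is used less efficiently than it could be. If treatment is tested by the group main effect, a visit at which no treatment effect can exist is averaged in. The supplement does not say which term is the treatment test.

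Two further features deserve attention: the stratification factors are absent, and the classical form of this ANOVA needs a value at every visit from every patient it uses.

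**Working it through.** **What time means.** The same model is applied to reactivity scores. A reactivity score is the Stroop level minus the mean of the two resting periods, so there is one number per session. A within-subject factor for it can therefore only be visit. With measurement before and after treatment, one level of that factor must be the pre-treatment visit. The word baseline in the model sentence refers to the resting periods within a session, not to t0, and the argument does not rest on it.

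**Inputs.** The protocol gives no effect size, standard deviation, correlation or missing-data rate for HRV, so there is no HRV figure to reproduce. Assumed: equal variance (set to 1) at both visits, correlation r between t0 and t1, and an illustrative effect d = 0.5. The 88 per arm is taken from section 9.2.

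**Precision, two visits.**
- Group-by-time (change score): variance 2(1 − r).
- Adjusted for t0 (ANCOVA): variance 1 − r².
- Ratio: (1 − r²) / [2(1 − r)] = (1 + r)/2.

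| r | ratio | n per arm under ANCOVA matching 88 under change scores |
|---|---|---|
| 0.4 | 0.70 | 88 × 0.70 = 61.6 |
| 0.5 | 0.75 | 66.0 |
| 0.6 | 0.80 | 70.4 |
| 0.7 | 0.85 | 74.8 |

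The variance is thus 15 to 30% lower for r from 0.7 to 0.4. The ratio is below 1 for every r below 1.

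**Illustrative power.** Power = Φ(d / [s√(2/88)] − 1.96), where s² is the variance above. For the group main effect the visits are averaged, so d halves to 0.25 and s² = (1 + r)/2.

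| r | group-by-time | ANCOVA | group main effect |
|---|---|---|---|
| 0.5 | 91.3% | 96.9% | 48% |
| 0.7 | 99.0% | 99.6% | 44% |

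**Complete visits, if three are analysed.** Assume a share q is missing at each of t1 and t2.
- If the same patients miss both visits, the loss is q: 10% at q = 0.10, 20% at q = 0.20.
- If missingness is independent, the loss is 1 − (1 − q)²: 1 − 0.81 = 19% at q = 0.10, 1 − 0.64 = 36% at q = 0.20.

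The range is therefore roughly 10 to 36%. In a three-visit simulation with independent missingness of 10 to 20% per visit, ANCOVA on everyone seen at t1 had 0.69 to 0.61 (r = 0.5) or 0.76 to 0.69 (r = 0.7) of the variance of the complete-case change from t0 to t1.

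**Complete visits, if only two are analysed.** A patient without the post visit has no post-baseline value, so adjustment for t0 or a mixed model recovers essentially nothing for that patient.

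**The case against.** The strongest case on the other side has five parts.

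- *No exclusion is stated.* A reader might infer that every patient with a missing visit is dropped. Supplement 5 does not say so. Section 13 names only SAS or SPSS without a procedure, and the same factors can be fitted by likelihood to partial data. Handling of missing HRV may also sit in an analysis plan that is not shown. This stands: completer-only analysis is a property of the classical method, not a rule of this protocol.
- *No contradiction with intention to treat.* A reader might infer a conflict with section 9.7. That section defines the population by allocation and is silent on absent outcomes. An analysis requiring at least one post-baseline value also leaves out some randomised patients. This stands, and no breach is claimed.
- *The figures belong to different layouts.* The change-score equivalence is exact for two visits. With three, the interaction has two degrees of freedom. The larger losses of patients need three visits. This stands, so the figures above are kept apart.
- *It is only efficiency.* Under randomisation and with complete data, the group-by-time contrast is unbiased, and it is the usual treatment test in such a layout. The main-effect power would apply only if that term were chosen. At r = 0.7 the illustrative power gain is under one percentage point. This limits the size of the point, but the gain exists at any r below 1 and needs no new data.
- *Strata cancel.* Additive centre and setting effects, as in section 9.1, drop out of a within-patient change. This is true for the change contrast, so their omission is the weakest part of the point. They should be carried once the post-baseline value becomes the response.

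**Conclusion.** The point holds as an improvement available at no cost. Supplement 5 leaves pre-treatment HRV among the outcome levels. In the pre/post layout, adjusting for it would cut the variance of the arm contrast by 15 to 30%, given assumed correlations of 0.7 to 0.4 and equal variances. The treatment test should be named, because a group main effect would be diluted by t0.

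A loss of roughly 10 to 36% of patients would arise only if three visits are analysed, the classical complete-data form is used, and 10 to 20% are missing per post-baseline visit. None of this is fixed by the protocol. The documents do not support saying that the plan excludes incomplete patients or breaches its intention-to-treat rule.

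The disagreements over the HRV schedule (sections 4.1 and 7.2, Supplement 5) and over the covariates within Supplement 5 are plain on the page. The effect is confined to a secondary, mechanistic endpoint. The confirmatory analysis in section 9.1 is untouched.

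**What to change.** In Supplement 5, replace the ANOVA with a linear mixed model for post-baseline HRV. Include the t0 value as covariate, arm, visit, arm-by-visit, age, sex and the centre and setting terms of section 9.1. Use all available post-baseline values and report the arm contrast at each visit as the treatment test. If there is only one post visit, this reduces to ANCOVA with the same covariates.

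Reconcile the HRV visits across sections 4.1 and 7.2 and Supplement 5, and settle one covariate list in Supplement 5 (age, body mass index and breathing frequency, or sex and age).

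The cost is analysis wording and code. The t0 value is already planned, so no new data are needed.
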